### Data monitoring by RM between data collection points

These data are required to ensure that the Data Monitoring and Ethics Committee is provided with adequate information to form an opinion concerning trial safety:

Development of major fetal abnormality between randomisation and labour onset

Fetal death between randomisation and labour onset

Maternal death between randomisation and labour onset

Hospital admission

Each month the Trial Office will provide RMs in the 5 centres with a list of trial numbers for participants who are still pregnant. The RM will use these to access subjects' computer records to obtain the information listed above. In the event of a hospital admission the RM will assess whether or not a serious adverse event has occurred and act accordingly see below. If the RM enters a fetal death into the database, this will automatically prevent further infant follow up and the RM will liase with the mothers' obstetrician to determine whether or not asking for follow up information concerning smoking behaviour around the anticipated time of delivery is acceptable. Major fetal abnormalities will also be reported to the trial office who will review these individually before deciding whether or not the participant should be allowed to continue within the trial.

### Registration with Office for National Statistics

The Trial Office will "flag" participants (women and babies) with the Office for National Statistics (ONS) at birth to facilitate follow up. Each week during the 2 year follow up period, the ONS will inform the trial team of any post-neonatal (i.e. between 29 days and 2 years) or maternal deaths.

### Procedure for administering postal follow up questionnaires

(see Figure 2): After infant deaths, questionnaires will not be sent and, where maternal deaths are reported, infants' general practitioners will be consulted about the appropriateness of continued follow up. The Trial Office will send questionnaires directly to study participants using contact details provided at study recruitment. For non-respondents or where questionnaires are returned labelled "*not at this address*", the office will check participants' addresses by contacting infants' grandparents and, if necessary, the ONS. ONS will trace the infant or mother and provide details of the Primary Care Trust (PCT) which provides their NHS health services and the Trial Office will then contact the infant's general practitioner so that a questionnaire can be sent. To maintain contact between researchers and participants, study infants will be sent Christmas cards and first birthday cards.

**Figure 2 F2:**
[figure not shown]
Follow up of trial participants from delivery until infants' second birthdays.

### Follow-up 6 months after childbirth

A postal questionnaire, with one postal and one telephone reminder, will be used to collect the data items specified below.

### Follow-up 1 year after childbirth

Two weeks before infants' 1st birthdays, *parents *will be sent a questionnaire to collect the data items specified below. Two weeks later, all participating infants will be sent a 1^st ^birthday card with a questionnaire reminder for non-respondents.

### Follow-up 2 years after childbirth

i) *Parent questionnaire*: Two weeks before infants' 2^nd ^birthdays, we will dispatch to *parents *a questionnaire to measure child behaviour, development, hospital admissions, respiratory symptoms and maternal smoking behaviour. Two weeks later, all participating infants will be sent a 2^nd ^birthday card with a questionnaire reminder for non-respondents. The instrument uses standard questions to record parents' reports of infants' respiratory symptoms [21] and behaviour [22], developed from those used in the MRC-funded UK Oscillation Study [23], with reference to the evidence base for questionnaire design [24].

ii) *Health professional questionnaire*: At the same time as parents' questionnaires are dispatched, we will post participants' general practitioners (GPs) a health professional questionnaire (*HPQ*) to measure children's disability according to a standard definition. [25] This brief instrument is designed to be completed using medical records. Health professionals completing these questionnaires require relatively little knowledge of the patient and GPs will be asked to complete them. If GPs cannot complete HPQs, they will be asked to forward these to children's' health visitors (HV). We will use an initial postal and subsequent telephone reminder to GPs to obtain the required information. The HPQ questionnaire has been validated and used with GPs and HVs previously [26,27] and requests data that HVs collect during their routine clinical practice to provide external validation of parents'.

### Data collection

Here the specific items of data to be collected at different points during the trial are outlined.

#### a) Baseline (i.e. pre-randomisation) data collection

Although online forms will allow data to be inputted to an online database, a paper copy of data will be kept for audit purposes.

##### i) Mandatory enrolment data (i.e. required for randomisation)

The RM will collect the following data from participants immediately after obtaining informed consent. The RM **must **enter the following data items about participants to the online database **before **randomisation is permitted:

*DoB *(valid range equiv to age 14–50)

participant's initials

hospital number

*daily number of cigarettes smoked before pregnancy*[28]

*daily number of cigarettes smoked currently*[28]

*agreed gestational age at time of randomisation *(valid range 12^0^–24^6^) [estimated delivery date will be calculated automatically within database]

time elapsed since last cigarette

exhaled CO reading of at last 8 ppm

*blood sample requested *(for cotinine assay, DNA extraction & storage)

indication that patient has signed consent form

*indication that participant's contact details have been recorded on paper *(see below)

agreed quit date

##### ii) Remaining baseline data for online entry

The following data will be collected with above data and the RM will also enter this on to the online database but entering these variables will **not **be mandatory before online randomisation is permitted.

*NHS number *(for ONS registration)

ethnic group

age left full time education

*number of previous births beyond 24 weeks *(valid range 0–12)

*time to first cigarette of day *[29]

partner's smoking status

maternal height

maternal weight at booking appointment

saliva sample

##### iii) Baseline data stored on paper

These personal data will be recorded on paper to allow data protection as the internet is not a secure transport medium.

*Participant name and contact details *(including landline/mobile telephone number & postcode)

*previous surname(s) *– for ONS registration

*Participant's general practitioner and/or name of practice plus practice address grandparents' contact details*, including phone numbers

#### b) One month after quit date

RM collects data from those who return. Postal questionnaires sent from NTCT to those who do not. The following data are collected:

RM notes *whether or not follow up occurs *and the *date of any follow up*. RM also inspects participants' supply of patches to calculate the number used.

Smoked at all in the previous 24 hrs

*Smoked since quit date *(further details on outcomes form 1)

Exhaled CO reading

On how many days have patches been used?

On how many days (if any) have non-trial patches been used?

How many behavioural support sessions with NHS stop smoking services used (telephone & face to face)?

Saliva sample for cotinine estimation taken

#### c) Upon admission for childbirth

The following data are recorded by the RM or delivery suite staff:

Date of follow up/exhaled CO reading or saliva sample

Smoked at all in the 24 hrs prior to delivery

Smoked between quit date and delivery

One or both of, *i) exhaled CO reading & ascertainment date ii) saliva sample *(for cotinine)

On how many days have patches been used?

On how many days (if any) have non-trial patches been used?

How many behavioural support sessions with NHS stop smoking services used (telephone & face to face)?

i) These data obtained by RM from ***maternal ***or ***infant medical records before ***discharge. For reasons of data protection some personal infant details are recorded on paper rather than being transmitted over the internet to the trial database:

*maternal *

hypertension (>140/90) on 2 occasions (excluding labour)

miscarriage (between randomisation and 24 weeks)

labour onset (spontaneous, induced, no labour)

mode of delivery (SVD, instrumental, caesarean)

ante natal or post natal maternal hospital admission

*infant*

baby initials

D.O.B

Gender

Baby NHS number

*Prompt for RM to confirm full name and address and contact details of baby and to record these on paper *(see below)

Prompt for RM to make a new record of contact details if these have differed from previous (i.e. maternal) ones

baby hospital number

birth weight

Number of births

if multiple birth, indicate number and birth order

live or stillbirth?

cord ph < 7.0

Apgar <7 at 5 min

*Gestational age at birth *– to be calculated within database from gestation at recruitment

These infant personal details will be recorded on paper only:

baby name

baby address (inc postcode)

ii) These data obtained by research midwife from ***infant medical records after ***discharge:

If live birth? live on leaving hospital

ventilation > 24 hrs

necrotising enterocolitis

neonatal convulsions

admitted to special care

*intraventricular haemorrhage *(4 categories)

*congenital abnormality present (y/n). If y then free text to describe this*.

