### Outcome measures

These relate to smoking, fetal loss, fetal and maternal morbidity and health economic outcomes.

Primary end point: Self-reported, prolonged and total abstinence [19] from smoking or the use of any non-pharmacological nicotine containing substances between a quit date set within two weeks of randomisation and immediately prior to childbirth.

Prolonged abstinence cannot be comprehensively validated, but if participants report prolonged abstinence and are abstinent at ***both ***time points below, they will be considered tohave a positive primary outcome. This is **one **outcome requiring **three **different measures to be achieved.

i) Self reported smoking cessation for at least 24 hours before follow up at one month after quit date, ***validated by ***exhaled CO measurement [cut off 8 ppm [17]].

ii) Self reported smoking cessation for at least 24 hours before hospital admission for childbirth, ***validated by ***exhaled CO measurement [cut off 8 ppm [17]].

Secondary end points:

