### Follow-up immediately before childbirth

When participants are admitted to hospital whilst in established labour *prior to childbirth*, Delivery Suite staff will contact the research midwife who will visit participants to ascertain their self-reported smoking status and use of transdermal patches. Women who report abstinence from smoking in the previous 24 hours will be asked by the research midwife to perform exhaled CO testing and provide a saliva sample for cotinine estimation. The RM will have overall responsibility for data collection and will arrange with Delivery Suite staff for this to be obtained in her/his absence. The RM will telephone those missed whilst in hospital as soon as possible afterwards (within 2 weeks maximum) to collect smoking behaviour data. Where participants report smoking cessation, the research midwife will measure their exhaled CO readings and obtain a saliva sample for cotinine estimation, visiting women at home if necessary.

Further infant, fetal and maternal data will be obtained from medical records (*details below*)

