### General statistical analysis plan

#### a) Primary outcome measure

The proportion of women who report prolonged and total abstinence from smoking immediately before child birth will be compared between treatment groups by Chi-squared test, on an intention to treat basis (all those randomised) with smokers lost to follow up considered to have continued smoking. For this analysis, we will assume that women in each group use their allocated treatments as directed and no randomised participants will be excluded from analyses. Baseline data on smoking behaviour and demographic information will be compared between groups, and adjustment made for any differences, using logistic regression.

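### The 24-hour window, biomarker and timing for the delivery component of the primary endpoint differ between the endpoint definition, the delivery form and the follow-up procedure

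*Protocol article*

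**What the plan says.** Three sections of the protocol article describe the same measurement.

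- **Outcome measures.** The primary outcome is a single composite with three parts. A woman succeeds "if participants report prolonged abstinence and are abstinent at" both time points. The delivery part is "Self reported smoking cessation for at least 24 hours before hospital admission for childbirth", validated by exhaled CO with a cut-off of 8 ppm. No alternative biomarker is offered.
- **Data collection, c) Upon admission for childbirth.** The smoking item reads "Smoked at all in the 24 hrs prior to delivery". The validation item can be completed by one or both of "exhaled CO reading & ascertainment date ii) saliva sample". A separate item asks about any smoking from quit date to delivery.
- **Follow-up immediately before childbirth.** Women who report no smoking in the preceding 24 hours are asked to "perform exhaled CO testing and provide a saliva sample for cotinine estimation". For the others, "The RM will telephone those missed whilst in hospital as soon as possible afterwards (within 2 weeks maximum) to collect smoking behaviour data". Those who then report cessation have CO and saliva taken, at home if need be. No latest date is set for that reading.

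No section gives a cotinine cut-off for abstinence, or says how a saliva-only record or a post-birth CO reading is to be classed.

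**The concern.** This is one of the three parts that must all be met for a primary success, and the form does not collect what the definition requires. Two gaps affect classification.

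First, a woman with saliva but no CO has a complete form and no means of meeting the definition. This is foreseeable: the women are in established labour, and delivery suite staff collect the data when the research midwife is absent. The one-month list has CO and saliva as separate items, so the either/or choice is peculiar to delivery.

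Second, the endpoint stops immediately before childbirth, but the validating CO may be taken days or weeks after it. The Background says about two thirds of women who stop in pregnancy restart after the birth.

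If these cases are left open, they will be classed by later judgement, and more than one primary result could be defended. A CO reading or pre-admission question missed at delivery cannot be recovered.

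**Working it through.** **Step 1. The sections side by side**

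| Feature | Outcome measures | Delivery form | Follow-up section |
|---|---|---|---|
| 24 h window ends at | admission | delivery | time of contact |
| Biomarker | CO only | CO, saliva or both | CO and saliva |
| Latest date for reading | before childbirth (implied) | none; date recorded | none; contact within 2 weeks |

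**Step 2. What happens to individual women**

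- *Abstinent throughout, saliva only.* The form is complete. The CO validation in the definition is not met, and there is no cotinine cut-off to apply. Her class is undefined; read literally, she is not a success.
- *Abstinent to delivery, restarted, CO taken after the birth.* The reading may be at or above the cut-off, and she then fails on post-natal smoking.
- *Smoked up to delivery, then stopped, misreports, CO taken after the birth.* The reading may be clean, and she passes.
- *Abstinent throughout, either window.* She answers no to both wordings, so the window alone does not misclassify her.
- *Smoked before admission but not in the 24 hours before delivery.* She passes the form's 24-hour item, but fails on the quit-date-to-delivery item if she reports truthfully.

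The biomarker and timing gaps therefore matter for classification. The window gap matters little, but is still a contradiction.

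**Step 3. The plan's own power figure**

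Inputs from Sample size: control 16%, treatment 25%, 500 per arm, two-sided 5%, stated power 93%.

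Power = Φ{ [ |p2 − p1|·√n − 1.96·√(2·p̄·(1 − p̄)) ] / √(p1(1 − p1) + p2(1 − p2)) }, where p̄ is the mean of p1 and p2.

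With n = 500 and p̄ = 0.205: (0.09 × 22.361 − 1.96 × 0.5709) / 0.5674 = 1.575, so power = 94.2%. This agrees with 93% to within about a point. With a continuity correction, 93% power needs 495 per arm. The secondary statement also reproduces: 16% versus 23% gives 79.9% against the stated 80%. The sample size is not in error on this point.

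**Step 4. Illustration of size**

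The documents give no figure for true abstainers missed at delivery. Assumption: a share m is missed, equal in both arms, so each rate is multiplied by (1 − m).

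| m (assumed) | Rates | Difference | Power, 525 per arm | Power, 500 per arm |
|---|---|---|---|---|
| 0 | 16.0% v 25.0% | 9.0 points | 95.2% | 94.2% |
| 10% | 14.4% v 22.5% | 8.1 points | 92.4% | 91.1% |
| 20% | 12.8% v 20.0% | 7.2 points | 88.4% | 86.9% |
| 30% | 11.2% v 17.5% | 6.3 points | 83.0% | 81.2% |

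The ratio of rates stays at 25/16 = 1.56 throughout; only the difference and the power shrink. The 525 column takes no account of the planned 5% loss to follow-up, which the analysis counts as smoking.

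**The case against.** The strongest reply is that the sections can largely be read together. The follow-up section asks every woman reporting abstinence for both samples, so the form's either/or may only be a recording minimum. Women missed in hospital are to be reached as soon as possible. The Background's two thirds has no time frame and cannot be applied to two weeks. Women are seen in established labour, so admission and delivery will usually be close, and the quit-date-to-delivery item catches reported earlier smoking. All of this stands, and it limits the consequences. It does not supply a rule for a woman with saliva only, or a latest date for CO.

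Three stronger readings are tempting, but the text does not support them.

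- *That true quitters are misclassified as smokers.* They can be, but nothing says saliva-only women count as smokers. The analysis section imputes smoking only to those lost to follow-up, and a woman who gave a report and a sample is not clearly lost.
- *That every error dilutes the treatment contrast.* A late CO reading can err in either direction.
- *That the analysis drops validation, because it compares "The proportion of women who report prolonged and total abstinence from smoking immediately before child birth".* The abstract calls the primary outcome biochemically validated, and Outcome measures requires validation at both time points. The analysis text abbreviates an endpoint already fixed.

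**Conclusion.** Wrong as written. The endpoint definition, the delivery form and the follow-up procedure contradict each other on when the 24-hour window ends and which biomarker is needed, and none sets a latest date for a post-birth CO reading. A saliva-only record completes the form but cannot meet the endpoint as defined. A post-birth CO reading does not validate abstinence before childbirth, and can err either way.

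How many women this affects cannot be derived from the document. The fall in power from about 95% to 92–83% (525 per arm), or from 94% to 91–81% (500 per arm), rests wholly on the assumed 10% to 30% missed equally in both arms. It shows scale and is not a forecast. Even its worst case leaves power above 80%. The case for acting rests on an undefined class for some primary outcomes and on data that cannot be collected afterwards, more than on lost power.

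**What to change.** Reconcile the three sections before recruitment starts.

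1. **One reference time.** Reword the form's smoking item to the 24 hours before admission, as in Outcome measures, and use the same wording in the follow-up section.
2. **One validation rule.** Make CO a required item at delivery, matching the endpoint. Otherwise, state before unblinding how saliva-only records are classed and with what cotinine cut-off.
3. **A time limit.** Set the latest date after birth at which a CO reading can count towards the endpoint, and say how later readings are classed.
4. **A sensitivity analysis.** Repeat the primary comparison using only readings taken before delivery or within 24 hours after it, using the ascertainment date already recorded. The listed item is a date, so either define the limit in calendar days or add a clock time.

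Two further changes should not be made. Letting self-report override a failed post-birth CO test would remove validation where it is weakest. Choosing the biomarker by reported NRT use would tie outcome ascertainment to a post-randomisation variable that blinded women cannot report reliably for trial patches.

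The cost is wording changes to the protocol and form, slightly stricter data collection at delivery, and one extra analysis.

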#### d) Six months after delivery

The following data will be requested by postal questionnaire, dispatched from the trial office:

Smoking status

Length of maternal inpatient stay for delivery of > 24 hours duration (if any)

Any infant neonatal admission to special care

Length of any infant inpatient stay on special care

*Maternal use of NRT/NHS stop smoking services since childbirth*,

*EQ5D questionnaire *[20]

#### e) At 1 year after delivery

The following data will be requested: *smoking status, respiratory symptoms and infant hospital admissions for respiratory illness and other causes*

#### e) At 2 years after delivery

The following data will be requested:

***Parent questionnaire**** – Smoking status, infant behaviour, development, respiratory symptoms and hospital admissions*.

***Health professional questionnaire**** – Child's disability*

### Interventions

Details of NRT patches are given earlier in this document and details of behavioural support follow. The first behavioural support session will be provided at recruitment by a research midwife who has been trained in smoking cessation methods in accordance with national standards [30] and who has dedicated time for this task. Models of behavioural support that are effective in pregnancy vary greatly[7] and in non-pregnant subjects, behavioural support following very different psychological models are all equally effective [31]. We will, therefore, standardise the first support session to include information on:

i) the harmful effects of smoking in pregnancy

ii) the role of nicotine addiction in sustaining smoking

iii) how to use NRT (including safety concerns)

iv) coping with withdrawal symptoms.

Support will be specific to the needs of pregnant women and may involve:

i) enlisting partner support

ii) a partner quit attempt

iii) ensuring that the partner has information about smoking cessation services

Study midwives will use brief cognitive – behavioural counselling, combining components from effective counselling strategies that are effective [31], such as:

i) providing structure to quit attempts

ii) agreeing a "contract" for any attempt

Counselling will be delivered in a manner that is consistent with routine clinical practice, using a format similar to that which has been effectively applied within routine ante natal care in the US [32]. A quit date which is within 2 weeks will be agreed and participants will be instructed to start using patches on this date.

Local NHS stop smoking services will provide up to 5 *subsequent behavioural support sessions*. These follow up sessions will reinforce women's reasons for quitting and strategies for success. A standardised approach to follow up support sessions is important and NHS stop smoking service staff will be orientated towards this.

